## Methods

### Trial Design

We will conduct a prospective, 2-group crossover RCT with a 1:1 allocation ratio to either the intervention (VR-PAT gameplay) or the control (VR headset turned off) for the first laser appointment. Participants will crossover to the opposite group at their second laser appointment. Pain, anxiety, and VR engagement (for those in the intervention group) will be assessed after each research appointment, spaced approximately 6 to 8 weeks apart. The findings will be reported based on the CONSORT (Consolidated Standards of Reporting Trials) guidelines. This protocol is reported in accordance with the SPIRIT (Standard Protocol Items: Recommendations for Interventional Trials) guidelines (Checklist 1).

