### Participant Timeline

Study enrollment at NCH—patients will be recruited prior to their first sequential dermatologic laser procedure. After consent and assent (if applicable) are obtained, patients will be randomized to either the VR-PAT intervention or the control group. A research associate will collect background information, such as demographics, anxiety levels, and prior video game experience, before randomization. VR-PAT instructions will be provided to the intervention group prior to participation.

Laser procedures at NCH (n=2 visits)—patients will receive their laser procedure as usual. Participants in the intervention group will wear the Pico headset and play the VR-PAT during their procedure. Participants in the control group will receive their laser procedure while wearing the VR headset (without the game). A researcher in the laser treatment room will observe the procedure and document, for the intervention group, the amount of time spent playing the VR-PAT, whether the participant declined to use it, and the number of interruptions of VR. Following the procedure, a different researcher (blinded to the group) will ask both groups of participants about their pain experience and satisfaction with the game. This process will be repeated once for each participant, as they will cross-over to the opposite intervention group at their next laser procedure.

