### Randomization and Blinding

A block randomization scheme with a block size of 4 will allocate participants to 1 of the 2 intervention sequences (VR-PAT followed by control or control followed by VR-PAT) at a 1:1 ratio without stratification. We chose a block randomization strategy to avoid imbalances in allocation to the intervention at the first visit in case we were unable to recruit our planned sample. The randomization scheme was developed and uploaded to a study-specific REDCap (Research Electronic Data Capture; Vanderbilt University) project by the project manager. Study participants are randomized into intervention sequences after signing consent and completing the baseline survey. Research recruiters and participants are not aware of the intervention assignment until the participant is randomized in REDCap.

We cannot blind the participants or the clinical team to the assigned intervention since the headset will either be turned on or off. The researcher who randomized the participant and observed the laser procedure will not be blinded, but a second researcher, who is blinded to the intervention group, will collect pain ratings and anxiety post procedure. The second researcher will wait in a different room during randomization and the laser procedure, and the first researcher will remind the participant at the end of the laser procedure to keep their group a secret until they are asked. The study biostatistician will also be blinded to the intervention group while performing analyses on the primary outcome. The data will be blinded by removing labels such as “VR” and “Control” and replacing them with unidentifiable letters (eg, “A” and “B”). The biostatistician will need to be unblinded for secondary outcomes, as only participants in the intervention group will answer the VR experience questions.

The blinded researcher will need to be unblinded after pain and anxiety ratings are obtained, as those in the control environment will not be able to answer the VR experience questions. The researcher will become unblinded by asking participants whether they played the game. The biostatistician will also be unblinded for full analyses by being provided with the full dataset, including complete data labels and VR questions. This unblinding will take place after the primary outcome analysis has been completed.

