### Adverse Events and Oversight

Participants playing the VR-PAT game will be asked to answer the question, “Did the game make you feel not well? If yes, please explain.” Study coordinators will carefully review the collected data for any adverse events reported during the study intervention and will immediately report this information to the project manager. The principal investigators will determine how serious the event was, whether it was related, and if it was unexpected. All serious adverse events will be reported immediately to the sponsor and the IRB. During recruitment, participants will be informed of which simulator sickness symptoms to be aware of and advised that if they occur, the laser procedure can be paused to remove the headset and use the standard eye protection available. All participants will also receive a direct phone number for the research principal investigator to report adverse events.

This trial will be overseen and coordinated by the co–principal investigators and a project manager. We will have at least 1 researcher to assist with screening, recruitment, consent, and data collection. The research principal investigator and project manager meet weekly to discuss the project, including recruitment updates, challenges, and any reported adverse events. There is no specific steering committee for this study.

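### Assessor blinding is secured for the first visit only: the assessor learns the arm at the end of visit 1, the crossover fixes visit 2, and no safeguard between visits is stated

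*Protocol article*

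**What the plan says.** Under Randomization and Blinding, the article concedes that participants and clinic staff cannot be blinded, and relies on a separate assessor: "a second researcher, who is blinded to the intervention group, will collect pain ratings and anxiety post procedure". That person stays in another room during randomization and the procedure, and the participant is reminded not to reveal the group. The same section then plans the unblinding: "The blinded researcher will need to be unblinded after pain and anxiety ratings are obtained". The reason given is that control participants cannot answer the questions about the VR experience. The method is direct: "The researcher will become unblinded by asking participants whether they played the game".

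The design is a two-period crossover. "A block randomization scheme with a block size of 4 will allocate participants to 1 of the 2 intervention sequences", and Trial Design adds: "Participants will crossover to the opposite group at their second laser appointment". Participant Timeline describes the post-procedure interview by a different, blinded researcher and then says: "This process will be repeated once for each participant, as they will cross-over to the opposite intervention group at their next laser procedure".

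The limitations in the Discussion acknowledge expectation bias among participants and clinicians. Assessors are not mentioned.

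**The concern.** Every protection described works within a single visit: the separate room, the reminder to keep the group secret, and taking the ratings before asking about the game. None deals with what the assessor carries from visit 1 to visit 2. In a parallel-group trial, unblinding after the last rating would do no harm. In a two-sequence crossover, what is learned after visit 1 is the assignment for visit 2.

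At stake is a stated property of the primary data. The pain ratings are primary outcomes and are obtained in person by this researcher. The primary pain analysis is paired, so each completer's difference contains one visit-2 rating. A reader of the eventual report would take assessor blinding to cover both visits, and the limitations section does nothing to correct that.

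**Working it through.** The article gives no figure to reproduce. The check sets its statements side by side and then counts.

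**Step 1: what the assessor learns at visit 1.** The assessor asks every participant whether they played the game (Randomization and Blinding). Yes points to VR-PAT and no points to control, so either answer is informative. The one exception is a participant assigned to VR-PAT who declined it, whose answer shows the condition received rather than the one assigned.

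**Step 2: what that implies for visit 2.** Two sequences are possible: VR-PAT then control, or control then VR-PAT. Once the visit-1 arm is known, one sequence remains, so the visit-2 assignment is known before any visit-2 rating is taken.

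**Step 3: whether anything breaks the link.** Three arrangements would do so: a different assessor at visit 2 with no access to visit-1 information, masking of visit-1 records from assessors, or giving the VR-experience questions to someone else. The article states none of them. It says only that the process is repeated.

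**Step 4: how many ratings could be affected.** Inputs from Results: 44 participants completed visit 1 and 40 completed both visits.

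- Post-procedure rating sessions among completers: 40 × 2 = 80.
- Let f be the share of visit-2 sessions rated by someone who knew the visit-1 arm. The documents do not give f. Sessions affected = 40 × f.
- f = 0: 0 of 80. f = 0.5: 20 of 80 (25%). f = 1: 40 of 80 (50%).
- Paired VR-minus-control differences affected = 40 × f of 40, so between 0 and 40 of 40, because each pair has exactly one visit-2 member.
- Visit-1 ratings are taken before the question is asked, so this mechanism does not touch them.

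**Step 5: which outcomes are exposed.**

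| Outcome | Rated by | Exposed at visit 2? |
|---|---|---|
| Pain ratings and anxiety during the procedure (NRS) | Participant, asked by the second researcher | Yes, through interviewer influence |
| mYPAS at T2 (after the procedure) | Observer; the second researcher collects post-procedure anxiety | Yes, if that researcher scored it |
| mYPAS at T0 and T1 (before the procedure) | Observer; not assigned to the second researcher | Not shown |

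The visit-2 mYPAS test specified in Data Analysis uses T0 and T1 only. T2 at visit 2 enters through the broader wording of Primary Outcomes, which compares the change across all three time points between visits.

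**The case against.** The strongest reply is that the article never says the same person rates both visits. It describes a role, the visits are about 6 to 8 weeks apart, and staffing by visit is a detail that an article may leave to the full protocol. This stands, and it is why the counts are upper bounds. It does not remove the point, because the article sets out its blinding procedure in detail, including a planned unblinding, and that procedure secures masking for one visit only.

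A reader might infer that one person must have done everything from the staffing statement in Adverse Events and Oversight: "We will have at least 1 researcher to assist with screening, recruitment, consent, and data collection". That does not follow. It is a minimum and not a roster of assessors. Taken literally, it would rule out a separate assessor even at visit 1, whereas Participant Timeline and Randomization and Blinding require two researchers.

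A reader might also infer that the visit-2 mYPAS comparison as a whole is compromised. The specified test uses pre-procedure ratings that the article does not assign to this researcher, so the documents do not support that.

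Finally, pain is self-reported by participants who know their condition, and that source of bias is already disclosed. Assessor masking guards only against the additional influence of the interviewer. This also stands, and it limits the likely importance. It is tempting to express the bias as a fraction of the 1.4-point lower benchmark under Sample Size. The documents give no interviewer effect, however, and the primary pain analysis uses a rank-based composite of pain and medication use, so NRS points do not carry over to it.

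**Conclusion.** As described, assessor blinding is secured for visit 1 and not for visit 2. Any assessor who meets the same participant again, or can see visit-1 information, knows the visit-2 assignment before rating. Up to 40 of 80 post-procedure sessions among completers (50%) and up to 40 of 40 paired differences could be affected. Those limits assume that such an assessor rated every visit 2; the true number is 0 if a masked assessor always did. The direction and size of any bias cannot be obtained from the documents.

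The stronger statement, that blinding failed at visit 2, is not supported, because the article does not show who rated it. What is supported is that the blinding claim reaches further than the procedure behind it, and that the limitations omit assessors.

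**What to change.** Data collection is complete and analysis is in progress, so for this trial the change lies in reporting and analysis.

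1. From the visit records, establish who took the post-procedure ratings at each visit and whether that person knew the visit-1 arm. State that assessor blinding holds at visit 1, and at visit 2 only where the records show an assessor without that knowledge.
2. Add assessors to the expectation-bias limitation in the Discussion.
3. Before the unblinded analysis, pre-specify a sensitivity analysis of the pain and post-procedure anxiety effects restricted to masked ratings. If the same assessor was always used, this becomes a between-group comparison at the first visit. The plan already holds such a comparison for the composite score, but only in the event of a significant carryover effect.
4. In the protocol for the larger study, have the first researcher, who is already unblinded, ask the VR-experience questions after the ratings are complete. The second researcher then never learns the group.

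The cost is a review of records, a few sentences and one further analysis now, and a swap of tasks between existing staff later. The masked-only analysis will be less precise, because it drops visit-2 ratings and may lose the within-participant comparison. It should be presented as a check on the main result and not as a replacement for it.

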### Intervention

VR-PAT is the intervention for this RCT. VR-PAT is a standalone mobile health tool developed at NCH and does not require an internet or WiFi connection. The intervention is hosted on a Pico Neo 3 Pro Eye, which is a standalone VR headset that supports native eye tracking, enabling applications to gather real-time user feedback for behavior-based application control. Our VR game is the only application available on the headset and starts immediately upon pressing the power button, which ensures all participants play the VR game intended for this study.

During the laser procedure, participants will play the virtual game by slightly tilting their heads, thereby minimizing interference with the procedure while cruising on a boat and aiming for the snow-blowing statues floating along the riverbank. The statues will burst and emit snow if the participant correctly aims at them, and a thermometer placed at the front of the boat will show decreased temperatures as more snowflakes are blown. As feedback to reinforce continued engagement, a scoreboard placed beside the thermometer will show participants the number of statues they have activated. Additionally, as the temperature drops, snow and ice will start piling up on the boat and its surroundings, providing an enhanced “cooling” experience for dermatology patients. Audio from the headset provides surrounding and directionally-adaptive effects to match the progress of the game and the direction in which a participant’s head is turning, further enhancing the immersive experience of VR-PAT during dermatologic laser procedures. The active VR-PAT game can last indefinitely, so it can be used for the entire procedure without interruption.

Participants playing the VR will be advised to discontinue using the headset during a procedure if it causes motion sickness, headaches, nausea, or dizziness. The dermatologist will pause the laser procedure and switch the eye protection to one available in the outpatient clinic. Any adverse events resulting from participation will be noted and reported in the participant surveys.

The comparator, or control, for this study is the same VR headset without the game, displaying only a dark screen. This comparator was chosen to maintain the experience of wearing something on the face for both groups. Patients undergoing a laser procedure are required to wear eye protection, which can include adhesive eye patches that occlude the eyes and create a similarly dark environment.

Participants in either intervention will be allowed to use any pain or anxiety medication that the dermatologist deems appropriate. Any medications provided will be documented.

### Measures

All data will be entered directly into the REDCap database as it is collected. A second researcher will check the REDCap records after each visit, ensuring the completeness and accuracy of the data. Data collected for this study include participant data, legal guardian data, nurse data, observed measures, and medical record review.

#### Participant Data (Self-Reported)

Prior to randomization, participants will report their prior video game experience, including the type of video games played, frequency, and favorite games. Before the laser procedure, all participants (control and intervention visits) will self-report their anxiety state using the State-Trait Anxiety Inventory for Children [32] (ratings ranging from “not at all” to “very much”) and their current anxiety using the Numeric Rating Scale (NRS; 0‐10) [33]. After the procedure, the participants will answer the remaining survey questions assessing overall pain score (NRS 0‐10) [34,35], worst pain score (NRS 0‐10), time spent thinking about pain (NRS 0‐10), length of the procedure (in minutes), and anxiety during the laser procedure (NRS 0‐10). Those playing the VR-PAT game will report their experience with the VR game (degree of realism, fun, engagement, and satisfaction; NRS 0-10) and respond to qualitative questions about their preferences with the VR-PAT. Participants will also be asked to report any simulator sickness associated with the VR game and whether they would want to use the VR again for future laser visits outside of research. These data will be collected at each of the 2 laser procedure study visits.

#### Legal Guardian Data (Self-Reported when Participants are <18 y)

Before the laser procedure, all legal guardians will self-report their anxiety state using the short-form 6-item State-Trait Anxiety Inventory [36], with ratings ranging from “not at all” to “very much”. After the procedure, the legal guardian will report their perception of the participant’s pain by providing an overall pain score (NRS 0‐10) and a worst pain score (NRS 0‐10). These data will be collected at each of the 2 study visits.

#### Nurse Data (Self-Reported)

To assess the practicality and utility of the VR experience as a pain and anxiety management tool for dermatologic laser procedures, the nurses will report whether the distraction tool is helpful and whether it is easy to use during laser procedures (yes or no).

#### Observed Measures (Research Collected)

The Modified Yale Preoperative Anxiety Scale (mYPAS) [37] will be assessed at each laser procedure before entering the treatment room, before the procedure begins, and immediately following the procedure. This is a 5-item scale, with a score of more than 30 indicating anxiety. During the procedure, the researcher will document the start and stop times of the laser procedure, the start and stop times of the VR (if applicable), whether the participant declined to use the VR-PAT, and the number of voluntary interruptions of the VR-PAT.

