#### Primary Outcomes

Difference in self-reported worst pain, average pain, and time spent thinking about pain (NRS 0 [min]−10 [max]) between VR-PAT and control visits. These questions are asked at each visit and will be compared between the intervention and control visits.

Change in procedural anxiety (mYPAS observed by the researcher, 23.33 [min]−100 [max], with higher scores denoting higher levels of anxiety) is assessed at 3 time points: prior to entering the procedure room, prior to the procedure, and immediately following the procedure for each laser procedure. These differences will be compared before and after the procedure, as well as between the intervention and control visits.

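### The rater of the primary mYPAS anxiety outcome is never named; as staffed, the rating before the procedure appears to be unblinded and the rating after it could come from either researcher

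*Protocol article*

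**What the plan says.** Under Primary Outcomes, the anxiety entry opens "Change in procedural anxiety (mYPAS observed by the researcher". Under Observed Measures, the scale "will be assessed at each laser procedure before entering the treatment room, before the procedure begins, and immediately following the procedure". Data Analysis calls these time points T0, T1 and T2. Neither section says which researcher does the scoring.

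Two researchers are described. Participant Timeline places one with the patient: "A researcher in the laser treatment room will observe the procedure and document" VR use, refusals and interruptions. Randomization and Blinding gives that person's status: "The researcher who randomized the participant and observed the laser procedure will not be blinded". The same section describes the other: "a second researcher, who is blinded to the intervention group, will collect pain ratings and anxiety post procedure". It also keeps that person away at the key moments: "The second researcher will wait in a different room during randomization and the laser procedure". Participant Timeline gives the blinded person a narrower task, in which "a different researcher (blinded to the group) will ask both groups of participants about their pain experience and satisfaction with the game", and does not mention anxiety.

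The blind is then broken at the end of the visit: "The researcher will become unblinded by asking participants whether they played the game".

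The limitations in the Discussion accept that expectation may sway participants and clinicians. They do not mention the outcome assessor.

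**The concern.** The other primary outcomes (worst pain, average pain, time spent thinking about pain) are the participant's own ratings. The mYPAS is a researcher's judgement of behaviour, so it is the one primary outcome on which the assessor's knowledge of the arm acts directly. A rater who knows the arm and expects VR to calm the child can score a little higher before a dark-headset procedure or a little lower around a VR procedure, without intending to. Either would pass straight into the contrasts under Data Analysis. The visit 1 t test is one-tailed, so a shift towards VR pushes in the tested direction.

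A second problem arises if T0 and T2 are scored by different people. Their difference then contains a between-rater difference as well as a change in the child. If only one of the two raters knows the arm, that difference need not cancel between groups.

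**Working it through.** The plan gives no figure to reproduce. The sample of 40 rests on budget and patient volume, and no alpha, power or SD is stated. The main check is therefore to set the sections side by side.

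**Who can have scored what**

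| Time point | What the article fixes | What follows |
|---|---|---|
| T0, before room entry | No rater named; order relative to randomization at visit 1 not stated | Effectively blind at visit 1 if scored before randomization; otherwise unknown |
| T1, before the procedure begins | Unblinded researcher observes in the room; blinded researcher's stated task is post-procedure | Appears unblinded; an inference from staffing, not a statement |
| T2, immediately after | Blinded researcher collects anxiety post-procedure, instrument not named | Could be mYPAS by the blinded person, or only the self-reported 0-10 rating, with mYPAS left to the unblinded person |

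Observed Measures lists the mYPAS beside the start and stop times of the laser and the VR. The in-room researcher is the person placed to record those, which supports the T1 inference.

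**Which contrasts are affected** (Data Analysis)

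- Visit 1, change T0 to T1: both ratings lie outside the blinded researcher's stated role.
- Visit 1, change T0 to T2: T0 lies outside that role. If the blinded researcher scored T2 and the other scored T0, the change crosses raters.
- Visit 2, T0 and T1 between groups: both lie outside that role. T2, the one rating that the stated role could cover, is not used.

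So every planned mYPAS contrast uses at least one rating outside the blinded researcher's stated role.

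**Visit 2.** The crossover fixes the visit 2 condition once the visit 1 condition is known, and the second researcher learns the latter by asking. If the same person returns, no visit 2 rating by that person is blind. The article does not say whether a different person is used.

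**Illustration of sensitivity.** Assume no true effect, a rater shift of b SD towards VR, n per group at visit 1, a one-sided test and a normal approximation:

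false-positive rate = Φ(b√(n/2) − z), where z is the critical value.

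With n = 20, √(20/2) = 3.162. For alpha 0.05 (z = 1.645) and b = 0.2: 0.632 − 1.645 = −1.012, so the rate is 15.6%.

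| b (SD) | alpha 0.05 | alpha 0.025 |
|---|---|---|
| 0 | 5.0% | 2.5% |
| 0.1 | 9.2% | 5.0% |
| 0.2 | 15.6% | 9.2% |
| 0.3 | 24.3% | 15.6% |
| 0.5 | 47.5% | 35.2% |

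The 44 who completed visit 1, taken as 22 per group, give 16.3% in place of 15.6%. Both alpha values and all values of b are assumptions. The table shows how little shading is needed to matter. It does not estimate what happened.

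**The case against.** The strongest reply is that the rater is simply not named, and an article may leave the holder of the rating sheet to the full protocol. The blinded researcher is said to be elsewhere only during randomization and the procedure, and T1 comes before the procedure begins. T2 may well fall under the blinded researcher's post-procedure anxiety collection. At visit 1, Participant Timeline places some anxiety data before randomization, so T0 may precede any knowledge of the arm. The article also claims blind collection only after the procedure, so it makes no false promise about T0 or T1.

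Much of this stands. A reader might infer that the in-room mYPAS ratings are known to come from the unblinded researcher, or that they are biased towards VR. The documents support neither: the first is a strong inference for T1 and open for T2, and the second is plausible but undocumented. A reader might also point to the anxiety threshold of 30. If the scale has four 4-level items and one 6-level item (an assumption that fits the stated minimum, since (4 × 1/4 + 1/6)/5 × 100 = 23.33), one step on one item of each kind gives 23.33 + 5.00 + 3.33 = 31.67. That crosses 30, but no planned test splits scores at 30, so the crossing changes no planned result.

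What does not stand is that this is only omitted detail. The article allocates the two roles explicitly, starts the blinded role after the procedure, and then builds its mYPAS contrasts largely on ratings made before it.

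**Conclusion.** The point holds in this form: blinded, single-rater scoring of an observer-rated primary outcome is not secured. T1 appears to be unblinded, T2 is unclear, T0-T2 change may mix raters, and visit 2 is blind only if the assessor has not learned the visit 1 arm. The blinding described for anxiety is limited to post-procedure collection, and the limitations leave out the assessor.

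The size and direction of any bias cannot be obtained from the documents; the false-positive rates above depend on assumed shifts and alpha levels. The T1 conclusion rests on reading the described staffing as complete. A record showing that the second researcher scored T0 and T2 at both visits, unaware of the arm, would settle most of the concern. The matter is worth correcting even in a pilot, because its estimates are meant to inform a multisite study.

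**What to change.** **Design, for the next trial and for the protocol text.** Name the mYPAS rater and that person's blinding status at T0, T1 and T2 for each visit, and reconcile Participant Timeline, Randomization and Blinding, Observed Measures and Primary Outcomes. Have the second researcher score both T0 (before room entry, and before randomization at visit 1) and T2 (after the headset is off). At visit 2, use a person who has not learned that participant's visit 1 arm. Make T0-T2 change the lead mYPAS contrast, which means adding T2 to the visit 2 analysis if that visit is to contribute. Treat T1 contrasts as unblinded and supportive. Do not move T1 ahead of the reveal of the arm: with no arm known and no VR exposure, the visit 1 T0-T1 contrast would have nothing left to detect.

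**Data already collected.** Collection is complete, so only reporting and the weight given to each contrast can change. List who scored each time point at each visit and whether they knew the arm. Base the anxiety conclusion on contrasts scored blind by one rater where these exist, and label the rest unblinded. Settle this ordering before mYPAS results by arm are seen, or declare it as made afterwards. Add assessor bias to the limitations. The post-procedure 0-10 anxiety rating can be shown alongside, but it is self-reported by an unblinded participant and does not check the rater.

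**Cost.** Scoring T0 and T2 needs no additional role, but visit 2 may need a different person in the second-researcher role. T1 contrasts carry less weight, and the blinding claim for anxiety becomes narrower.
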